## Methods/design

Ethics approval was granted by the Research Ethics Board at the University of Toronto (protocol #44916). The study was registered with ClinicalTrials.gov (NCT06624930) on October 3, 2024 and the study protocol was developed using the SPIRIT (Standard Protocol Items: Recommendations for Interventional Trials) 2013 statement [44].

### Study design

This study is a two-armed, multi-site RCT, to examine the effects of PA + EC versus PA + BC on MVPA in people LWBC. A 6-month follow-up (T3) and 1-year follow-up (T4; 1-year follow-up from post-intervention) will take place after the intervention to address maintenance. The study flow is outlined in Fig. 1 and the study measurements, outcomes, and schedule are summarized in Table 1.

**Table 1 Tab1:** Outcome measures at each time point with time required for completion

Domain/Measure	Time Required for Completion	Baseline (month 0;T0)	Mid-point (month 3; T1)	Post-intervention (month 6; T2)	6-month follow-up (month 12; T3)	1-year follow-up (month 18; T4)
Eligibility		X				
Informed consent		X				
Group allocation (after completion of baseline, T0)		X				
**Interventions**						
*Intervention Group* - Physical Activity + Behavioral Counseling Group (PA + BC)						
*Attention Control Group* - Physical Activity + Exercise Counseling Group (PA + EC)						
**Measures**						
**Primary outcome**						
Physical activity (ActiGraph accelerometers)	Worn for 7 days during waking hours only	X	X	X	X	X
**Secondary outcomes**						
Quality of life (Functional Assessment of Cancer Therapy [FACT]-General, FACT-Fatigue, Fatigue subscale, EuroQol-5D)	20 min	X	X	X	X	X
Measures from the Multi-process Action Control (M-PAC) framework (affective attitudes, instrumental attitudes, injunctive norms, descriptive norms, and perceived control, behavioral regulation for physical activity, physical activity habits, exercise identity)	15 min	X	X	X	X	X
Physical function (i.e., 30-second chair stand, 6-minute walk test)	30 min	X	X	X	X	X
Demographic, medical and health history questionnaire	10 min	X				
Health economics (Health Services Utilization Inventory, iMTA Productivity Cost Questionnaire, Incremental Cost of Intervention)	20 min	X	X	X	X	X
Participant satisfaction questionnaire	5 min			X		
Adherence and compliance (Physical activity log)	5 min	assessed throughout intervention				
Fidelity and quality control (Fidelity checklists)	5 min	assessed throughout intervention				
Adverse events (Adverse events log)	5 min	assessed throughout intervention				

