Therefore, the primary purpose of this study is to compare the effects of delivering an entirely virtual 6-month supervised MVPA group plus standard exercise counseling (PA + EC) versus a virtual supervised MVPA plus motivationally-enhanced behavioral counseling (PA + BC) group on MVPA in people LWBC. We hypothesize that the PA + BC group will increase MVPA compared to the PA + EC group at mid-intervention (T1; 3 months), post-intervention (T2; 6 months), 6-month follow-up (T3; 6 months post-intervention), and 1-year follow-up (T4; 1-year follow-up from post-intervention). Secondary outcomes include: (1) to determine the effects and cost-effectiveness of PA + EC versus PA + BC on secondary outcomes, including changes in reflective, regulatory, and reflexive processes from the M-PAC, physical function, QoL and costs; (2) to examine the regulatory and reflexive mediators of the 6-month intervention on MVPA; and (3) to examine moderators of treatment efficacy in the PA intervention. We will compare across various demographics (e.g., intersection of age, sex, gender, ethnicity, body mass index), fitness (e.g., baseline PA), and clinical subgroups (e.g., cancer type), as well as adherence and intervention completion across groups. This study will address gaps in the PA maintenance literature to demonstrate: (1) changes in absolute values across behavioral performance of people LWBC, (2) an increase in their magnitude of effect on PA over time; [26] and (3) sex and gender differences in PA maintenance.

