Following all baseline testing delivered remotely (i.e., physical function), participants will be randomized to one of two groups: PA + BC or PA + EC (attention control). People LWBC in both groups will receive a tapered, home-based program lasting 1 hour for 3 days per week for the first 12 weeks, 2 days per week for week 13–18, and then 1 day per week for week 19–24 (54 sessions total). Qualified exercise professional (QEP)-led, group-based (~ 12 participants per class [55]) PA sessions completed at home via videoconferencing (i.e., Zoom), resistance bands, and an exercise mat will be provided for both groups. Consideration of the different cancer types are addressed through the tailored PA prescriptions and individual counseling sessions. Additional at home/unsupervised sessions will be prescribed, where people LWBC will be asked to complete one PA session on their own for weeks 13–18, and two PA sessions for weeks 19–24 (Fig. 2). Tracking and monitoring tools (i.e., Fitbits, PA logs) will be provided to ensure intensity and duration are met for both groups. A PA manual will be distributed to each participant as an ongoing resource, which will be developed separately for each of the two groups, with the behavioral counseling group containing more content (i.e., theory-based counseling). Sessions will be delivered by QEPs which encompasses graduate students in Kinesiology who are certified trainers with the Canadian Society of Exercise Physiologists (CSEP) or ACSM, as well as Registered Kinesiologists or Physiotherapists with experience working with people LWBC at the University of Toronto site for consistency. Training sessions/manuals will be provided for strict protocol adherence including core delivery components for the counseling sessions, cancer treatment information, PA safety and barriers, and quality control checklists.

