*Intervention Group - Physical Activity Group + Behavioral Counseling Group (PA + BC)-*The PA + BC group will receive a behavioral counseling support session with a QEP every two weeks during the intervention period (12 total). The support sessions will be 30–45 min and delivered via Zoom each week in either group or 1:1 format depending on the topic. The videoconference calls will incorporate tailored behavior change content from the M-PAC framework (Table 3; Fig. 2). Of the 12 video-conferencing calls, one session will target reflective processes (instrumental/affective attitudes), five sessions will target behavioral regulation (action planning, coping planning, social support, goal setting, emotion regulation), and four sessions will target reflexive processing (identity, habit). The remaining two sessions are “booster sessions” to revisit topics discussed. The importance of sustaining PA for clinical outcomes (e.g., fatigue) and PA logs will be stressed. At the end of the 6-month intervention, an individualized PA prescription will be provided based on their fitness level (adjusted throughout) to continue achieving the PA goal for the 6-month and 1-year follow-up.

*Attention Control Group ** Physical Activity Program + Exercise Counseling Group (PA + EC)-*The PA + EC group will receive the same frequency of group-based and 1:1 counseling support sessions via Zoom as PA + BC participants. However, the focus will be on PA training principles for proper PA technique, how to monitor intensity, and progress PA safely to achieve the PA guidelines. The support sessions will be 30–45 min and delivered via Zoom each week in either group or 1:1 format depending on the topic (Table 3; Fig. 2).

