**Fig. 2 Fig2:**
[figure not shown]
Overview of Study Components

**Table 3 Tab3:** Bi-Weekly videoconferencing topics for the supervised physical activity group plus behavioral counseling (PA + BC; intervention group) and supervised physical activity group plus exercise counseling (PA + EC; attention control group)

Week& Format	Description of Behavioral Strategies (PA + BC group)	Multi-process Action Control (M-PAC) Constructs for PA + BC Group Mapped to Behavior Change TechniquesUsed in Michie et al. (2013)^a^	Topics for Attention Control Group (PA + EC group)
2 Group	*Target M-PAC construct: Reflective processes (instrumental/affective attitudes)* Discuss the benefits of increasing physical activity for health and clinical outcomes, and how to make activity enjoyable	5.1 Information about health consequences 5.2 Salience of consequences 5.3 Information about social and environmental consequences 3.3 Social support (emotional) 5.6 Information about emotional consequences 7.5 Remove aversive stimulus 12.5 Adding objects to the environment	Physical activity guidelines
4 1:1	*Target M-PAC construct: Regulatory processes (goal setting)* Setting challenging, yet achievable goals using the SMART goal guidelines and developing rewards for achieving goals	11.1 Goal setting (behavior) 1.2 Problem solving 1.3 Goal setting (outcome) 1.8 Behavioral contract 2.3 Self-monitoring of behavior 2.6 Biofeedback 7.1 Prompt/cues 10.7 Self-incentive 11.2 Reduce negative emotions 13.4 Valued self-identity	Components of a physical activity training session
6 1:1	*Target M-PAC construct: Regulatory processes (action planning)* Action planning will be targeted by creating plans for increasing physical activity	1.1 Goal setting (behavior) 1.2 Problem solving 1.8 Behavioral contract 2.3 Self-monitoring of behavior 2.6 Biofeedback 7.1 Prompt/cues 10.7 Self-incentive 11.2. Reduce negative emotions	Physical activity intensity (e.g., heart rate training)
8 Group	*Target M-PAC construct: Regulatory processes* (self-monitoring) Discussion of how to monitor physical activity using wearables (e.g., Fitbits) and logs to keep track of progress towards goals	1.1 Goal setting (behavior) 1.2 Problem solving 1.4 Action planning 1.8 Behavioral contract 2.3 Self-monitoring of behavior 2.6 Biofeedback 7.1 Prompt/cues 10.7 Self-incentive 11.2 Reduce negative emotions 15.4 Self-talk	Signs and symptoms for stopping physical activity

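### Adherence is compared between arms using an activity log that is stressed and taught only in PA + BC, so differential logging can appear as a difference in adherence on this secondary outcome.

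*Protocol article*

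**What the plan says.** Table 1 (Secondary outcomes) gives the measure as "Adherence and compliance (Physical activity log"), assessed throughout the intervention. No other source for adherence is named in the article. The last paragraph of the Background lists the planned comparisons and ends them with "as well as adherence and intervention completion across groups".

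Under Study groups, the tools go to both arms: "Tracking and monitoring tools (i.e., Fitbits, PA logs) will be provided to ensure intensity and duration are met for both groups". The emphasis on them differs. The PA + BC paragraph states: "The importance of sustaining PA for clinical outcomes (e.g., fatigue) and PA logs will be stressed". The PA + EC paragraph has no such sentence; there, "the focus will be on PA training principles for proper PA technique, how to monitor intensity, and progress PA safely".

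Table 3 shows the same contrast. The week 8 session for PA + BC is self-monitoring: "Discussion of how to monitor physical activity using wearables (e.g., Fitbits) and logs to keep track of progress towards goals". In the same slot PA + EC covers "Signs and symptoms for stopping physical activity". No PA + EC topic title mentions logs.

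The supervised program tapers to "1 day per week for week 19–24 (54 sessions total"). Participants are also asked to do one session a week on their own in weeks 13–18 and two a week in weeks 19–24.

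**The concern.** An adherence measure should record what participants did in the same way in both arms. Here the instrument is also something the experimental counseling tries to change. Self-monitoring of behavior is a listed technique for PA + BC in weeks 4, 6, 8 and 10, and the week 8 session deals with logs by name. If PA + BC participants record a larger share of the sessions they complete, logged adherence rises in that arm without any extra exercise, and the log alone cannot separate the two explanations.

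Timing adds to this. Unsupervised sessions start in week 13, after PA + BC has had its self-monitoring session, and no class leader sees them. The Background also cites preliminary evidence that behavioral counseling may improve adherence over exercise counseling alone, so better recording in PA + BC would push the result in the direction the investigators expect.

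At stake is the secondary comparison of adherence between arms, and any reading of the trial that uses it to explain the effect on activity.

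**Working it through.** **Step 1. Session counts (Study groups, Table 2).**
- Supervised: 12 × 3 + 6 × 2 + 6 × 1 = 36 + 12 + 6 = 54, which reproduces the article's total.
- Unsupervised: 6 × 1 + 6 × 2 = 6 + 12 = 18.
- All prescribed: 54 + 18 = 72. Supervised share 54/72 = 75%; unsupervised share 18/72 = 25%.

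**Step 2. The arms side by side.**

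| | PA + BC | PA + EC |
|---|---|---|
| Logs and Fitbits supplied | yes | yes |
| Logs stressed in the arm's description | yes | not stated |
| Session on wearables and logs | week 8 | none listed |
| Nearest related content | self-monitoring technique in weeks 4, 6, 8, 10 | heart-rate intensity (week 6); progress feedback (from week 20) |

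Access is equal. Coaching on the instrument is not.

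**Step 3. Size if every session is taken from the log.** The article gives no adherence or logging rates, so these are assumptions: true adherence A is the same in both arms, a share L of completed sessions is logged, and an unlogged session counts as missed.

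Logged adherence = A × L, so the spurious difference = A × (L in PA + BC − L in PA + EC).

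With A = 0.70:
- Logging gap of 5 points: 0.70 × 0.05 = 0.035, or 3.5 points.
- Logging gap of 15 points (for example 95% against 80%): 0.665 − 0.560 = 0.105, or 10.5 points.

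With A from 0.60 to 0.80, the 5-point gap gives 3.0 to 4.0 points and the 15-point gap gives 9.0 to 12.0.

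**Step 4. Size if only the unsupervised sessions are taken from the log.** Assume supervised attendance is recorded correctly in both arms. Only 25% of sessions can then be affected:
- 5-point gap: 0.035 × 0.25 = 0.00875, about 0.9 points of total adherence.
- 15-point gap: 0.105 × 0.25 = 0.02625, about 2.6 points.

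**Step 5. What remains within the unsupervised part.** As a percentage of the 18 unsupervised sessions, the gap is still 3.5 to 10.5 points: 0.035 × 18 = 0.63 to 0.105 × 18 = 1.89 sessions per participant. That part should therefore be reported separately and read with caution.

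**The case against.** The strongest reply is that the arms differ in emphasis only. Both receive logs and Fitbits for the same stated purpose, PA + EC is taught to monitor intensity and gets feedback on progress, and Table 3 gives its topics by title alone, so some log guidance may sit inside them. Equal access is correct, and the point must not be read as saying that only one arm keeps logs. But the article does treat log-keeping as counseling content in one arm and not in the other.

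A second reply is that Table 1 is a summary. It omits the Godin questionnaire, which the text lists as a secondary outcome, so it is not exhaustive, and attendance may be used in the full protocol. The rule for blank logs may also be set there, and its absence from an article is no defect. This limits what can be said about size. It does not remove the choice that the article states, which is the log.

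A reader might infer three stronger things, and the documents support none of them:
- *That the log will favor PA + BC.* Uncoached logs could be filled in from memory and over-report. That participants complete the logs themselves is implied, not stated.
- *That the distortion is about 10 points.* That figure needs an assumed 15-point logging gap, unlogged sessions counted as missed, and all 72 sessions taken from the log, although 75% of them are led by an exercise professional.
- *That the main result is compromised.* The primary outcome is accelerometer-measured activity, and data collectors are blind to allocation.

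Accelerometry also gives a partial check on the adherence result, but time in moderate-to-vigorous activity over a 7-day wear period is not attendance at prescribed sessions.

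**Conclusion.** The concern holds in a limited form. The article fixes the log as the only named adherence measure, plans to compare adherence between arms, and makes log-keeping part of the treatment in one of them. A difference in logging can therefore appear as a difference in adherence.

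Neither the size nor the direction is known. Under the assumptions in the working (70% true adherence in both arms, unlogged counted as missed, a logging gap of 5 to 15 points), the spurious difference is 3.5 to 10.5 points if the log supplies all 72 sessions and about 0.9 to 2.6 points if it supplies only the 18 unsupervised ones. The consequence is confined to this secondary outcome. The change is still worth making, because three quarters of the sessions can be recorded in a way that the counseling does not influence.

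**What to change.** In Table 1, base adherence to the 54 supervised sessions on class attendance recorded by the exercise professional in both arms, and make this the between-arm adherence comparison.

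Report the 18 unsupervised sessions separately from the log, with Fitbit data as support only. Fitbit data cannot simply replace the log, because the same week 8 session coaches PA + BC on wearables as well. Give both arms identical instructions and prompts for keeping the log, and state that log and Fitbit completeness may differ by arm because PA + BC is coached on both.

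The cost is an attendance entry per class and some extra data handling. Identical prompts slightly narrow the contrast in self-monitoring between the arms, but the PA + BC counseling content can stay as it is.

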### Recruitment procedures

#### Participant eligibility

Eligibility for this study include those who are: 1) ≥ 18 years of age, 2) have a confirmed diagnosis of cancer of any type (Stages I to III; localized), 3) have completed primary cancer treatments within 5 years, 4) at least 12 weeks post-surgery and/or 6 weeks post-radiation, 5) are proficient in English, 6) are physically inactive (self-report < 90 min of MVPA/week) [45], 7) ambulate in daily life with minimal gait aid use (i.e., aid versus no aid), 8) have access to and can operate a smartphone/tablet/computer with a webcam for videoconferencing and a Bluetooth connection, 9) have access to the internet, and 10) have no cardiac contraindications (e.g., unstable angina, heart failure, coronary artery disease, diagnosed abnormality of heart rhythm). Participants are excluded if they: (1) have a medical condition that prohibits PA (e.g., joint restriction or weight bearing precautions), (2) have uncontrolled comorbidities or cardiovascular contraindications that would increase risk associated with supervised and unsupervised PA (e.g., cardiac contraindications, severe arthritis, recent fall within last 6–12 months), (3) advanced cancer (i.e., Stage IV; metastatic), and (4) do not intend to live in Canada for the next 18 months.

#### Participant recruitment

A total of 236 participants (*n* = 118 in each study group) will be recruited through listservs and flyers distributed in the community and posted in local cancer organizations. Recruitment will be performed through word of mouth and advertisements both online and through local community cancer support centers.

#### Screening procedure and informed consent

Potential participants will be screened by study staff over the phone to determine if they meet the eligibility criteria. Physician’s clearance for participation will be sought following PA guidelines outlined by American College of Sports Medicine (ACSM) and the National Comprehensive Cancer Network Survivorship Guideline [46, 47]. If the participant is eligible and willing to consent, study staff will review the informed consent process with the participant.

**Fig. 1 Fig1:**
[figure not shown]
Study Flow Diagram

#### Randomization

Participants will be 1:1 randomized to either the PA + EC or the PA + BC group. Randomization will be performed using a stratified randomization scheme in the REDCap Randomization Module after baseline assessments. The sequence will be random permuted blocks of varying sizes, stratified by prior chemotherapy (yes versus no), age (< 65 versus ≥ 65 years), and sex (female versus male) to balance treatment characteristics that would potentially impact the severity of fatigue and intervention response [46]. Randomization codes will be kept in a pre-made digital file that is separate from other study records. Only the research co-ordinator will have access to the randomization codes. Following randomization, the research co-ordinator will update the randomization log to indicate the code has been used and include the ID number of the participant it was assigned to.

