#### Blinding

All participants will be partially blinded to group assignment as they will not be told which study group will yield greater benefits as both groups receive supervised PA. The research co-ordinator will be responsible for scheduling all data collection assessments with research assistants (RAs) who are blind to group allocation. An independent group of RAs (separate than those who are engaged in data collection) will conduct the behavioral counseling and group webinars.

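### The one role with access to the randomization codes also schedules assessments, and the protocol does not say that unused codes are hidden from it

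*Protocol article*

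**What the plan says.** The Randomization section of the Protocol article first names the system: "Randomization will be performed using a stratified randomization scheme in the REDCap Randomization Module after baseline assessments". It describes the sequence as follows: "The sequence will be random permuted blocks of varying sizes, stratified by prior chemotherapy (yes versus no), age" (under 65, or 65 and over) and sex.

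The same section then turns to custody of the codes: "Randomization codes will be kept in a pre-made digital file that is separate from other study records", and "Only the research co-ordinator will have access to the randomization codes". Once a participant has been randomized, "the research co-ordinator will update the randomization log to indicate the code has been used and include the ID number of the participant" to whom it was given.

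The Blinding section adds a further duty for the same role: "The research co-ordinator will be responsible for scheduling all data collection assessments with research assistants (RAs) who are blind to group allocation". Table 1 places group allocation after completion of T0. Under Screening procedure and informed consent, screening and the consent discussion are assigned to study staff. The co-ordinator is neither named there nor excluded.

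**The concern.** Allocation concealment requires that nobody who can influence entry into the trial, or its timing, knows the next assignment. Here one role has exclusive access to a list prepared in advance and also books the assessment that must be finished before a participant can be randomized. The custody rule separates the codes from other records. It does not separate them from the person running the appointment diary.

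If that person can read upcoming assignments, bringing a baseline visit forward or putting it back could change which arm a participant receives, deliberately or not. In a trial of behavioral counseling, the characteristics most likely to prompt such a choice, such as motivation or readiness to change, plausibly affect MVPA and are not fully captured by the listed covariates. What is at stake is selection bias in the primary comparison of the two groups.

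**Working it through.** The protocol gives no figure to reproduce on this point, and the conclusion depends on no sample size, power or effect size. The check sets the statements side by side.

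1. **Who can see the codes.** The research co-ordinator, and nobody else (Randomization). This is a stated rule, not a detail left out.

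2. **When the codes exist.** Before enrolment, since the file is pre-made (Randomization). Unused codes are therefore in the file while participants are being scheduled.

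3. **Who controls timing.** The co-ordinator schedules assessments (Blinding). Baseline is one of them, and randomization comes after it (Randomization; Table 1). The role therefore has some influence over when participants become ready for randomization and in what order.

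4. **Which source governs.** The section names the REDCap module, then a separate file and a log of used codes, without saying how they relate. There are two readings:
   - The file is the allocation table loaded into REDCap, or a copy of it. Assignment is then made by the module, but the co-ordinator's access to the file bypasses the concealment that the module can provide.
   - The file is the working source of assignments. The trial then runs from a list held by the person who schedules.

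   On either reading, concealment from the co-ordinator depends on whether unused codes in the file reveal the arm. The article does not say.

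5. **What the stated safeguards cover.**
   - *Varying block sizes.* They make it hard to infer the next assignment from past ones, which the co-ordinator knows from the log. They give no protection against reading the next assignment directly. There are 2 × 2 × 2 = 8 strata, and chemotherapy history, age group and sex can all be known before randomization. If the file is ordered by stratum and shows the arm, the next code for a given participant can be looked up.
   - *Blinded assessors.* They protect the measurement of outcomes, not entry into the arms.
   - *Covariate adjustment* (Statistical analysis: baseline PA, age, sex, treatment and cancer type, given as examples). It reduces imbalance on those factors and leaves imbalance on unmeasured ones.
   - *Randomization after baseline.* It narrows the route, because eligibility and consent are settled earlier. It leaves the order and timing of T0 completion open.

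6. **Size.** With 1:1 allocation, someone who sees neither the list nor past assignments guesses the next arm correctly with probability 1/2. If the file shows upcoming assignments, that probability is 1 for its holder. This holds only under that condition. Going from there to a bias in minutes of MVPA would need the frequency of reordering and the prognostic difference between the participants affected. The document gives neither.

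**The case against.** The best defence is that the article says assignment is performed in the REDCap module, and that the only act it gives the co-ordinator in connection with assignment is logging a code afterwards. The file may simply be the table prepared for upload, with a log kept for audit. Any allocation table is made in advance, so its existence is no fault. The file's layout is not described, and nothing says that a code shows the arm. A condensed article may also leave REDCap user rights to the full protocol.

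Much of this stands. A reader might infer that the co-ordinator opens the list, draws each assignment from it and knows the next arm with certainty in every stratum. The documents do not support that: readability of future assignments and use of the file to assign are both inferences. A reader might also infer that the co-ordinator controls who enters the trial. The article does not show that either. Screening and consent belong to study staff, physician clearance is sought, and the documented lever is scheduling. Even that lever is partial. Baseline includes a mailed accelerometer worn for 7 days and returned by post, so the order of T0 completion depends partly on participants and the mail. Changing an allocation would also require changing the order among participants in the same one of the 8 strata.

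The defence does not remove the core. Sole access to the codes and responsibility for scheduling are both stated, and they belong to the same role. Leaving user rights to another document would excuse silence, but here the article states who has access, and the role it names is one that should not see unused codes.

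**Conclusion.** The point holds in conditional form. The protocol puts exclusive access to the randomization codes and the scheduling of the pre-randomization baseline in one role. It does not say that unused codes are masked, or whether the file or the REDCap module determines assignment. If the file shows upcoming assignments, allocation is not concealed from someone who can influence the order and timing of randomization, and the safeguards described do not close that gap.

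This rests on two assumptions: that access to the codes includes unused ones in a form that shows the arm, and that scheduling has some effect on the order in which participants complete T0. The size of any bias cannot be derived. Nothing in the document shows that concealment has been breached, and this point does not claim that it has. It is a weakness in the stated custody rule that should be corrected before further participants are randomized.

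**What to change.** Revise the Randomization section to state four things:

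1. The REDCap Randomization Module is the only source of assignment.
2. The allocation table is generated, uploaded and held by a team member with no role in recruitment, scheduling or participant contact.
3. The co-ordinator has no access to unused codes, and REDCap user rights enforce this.
4. Each assignment is revealed only after T0 has been marked complete for that participant.

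The log completed after randomization can stay. It is an audit record of assignments already made, and the problem is access to unused codes, not the log.

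The cost is a small change of user rights and wording, plus handing custody of the table to someone else. The article identifies no team member without participant contact, so it is an assumption that one is available within the existing team. Sample size, visits and interventions are unchanged. For participants already randomized the change has no effect, so the date on which custody moves should be recorded.
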